### *Induction variables*

During anesthesia induction, patient's position and use of CPAP or NPPV will be documented.

### *Intra-operative variables*

During the intra-operative period, the following variables will be recorded (variables are to be measured after induction, hourly and immediately before and after recruitment maneuvers):

- Duration of anesthesia procedure; from tracheal intubation to extubation *or* exit from operation room (in case patient remains on mechanical ventilation); minutes
- Duration of surgical procedure from incision to closure; minutes
- Operation classification; clean, clean-contaminated, contaminated *or* dirty according to Berard and Gandon 
- Surgical approach: laparoscopic surgery (specify intraabdominal pressure); assisted laparoscopic (specify intraabdominal pressure), open, conversion from laparoscopic to open
- Patient position during surgery: supine, Trendelenburg, reverse Trendelenburg, lithotomy, sitting position
- Types and total doses of anesthetics; inhalational, intravenous or balanced + dose
- Neuraxial anesthesia; if yes: specify epidural, plexus, peripheral
- Antibiotic prophylaxis; if yes: specify regimen
- Ventilator settings, hourly:
  - Peak and plateau pressures; cmH2O
  - PEEP; cmH2O
  - Tidal volume; ml
  - Respiratory rate
  - Inspiration to expiration ratio
  - Inspired oxygen fraction; %
  - Peripheral oxygen saturation; %
  - End-tidal fractions of CO2; mmHg
- Noninvasive systolic, diastolic and mean arterial pressure; mmHg
- Vasoactive drugs; if yes: specify type and dose
- Heart rate
- Temperature at end of surgery; °C

- Fluid requirements (crystalloids, artificial colloids, and albumin; specify type and amount)
- Transfusion of packed red blood cells, fresh frozen, plasma frozen within 24 hours (FP24), fibrinogen, cryoprecipitate, PPSB and platelets in the preceding six hours; if yes: specify type and number of transfused units/amount
- Blood loss; ml for whole duration of surgery
- Urine output; ml for whole duration of surgery

Protocol adherence, specify if any deviation from the protocol:

- Hypotension (BPsys < 90mmHg) unresponsive to fluids and/or vasoactive drugs
- New arrhythmias unresponsive to intervention (according to ACLS-Guidelines)
- Need for a dosage of vasoactive drugs at the tolerance limit
- Need of massive transfusion (replacement of >50% of blood volume in 4 hours to maintain Hct > 21% (Hb > 7mg/dl)
- Life-threatening surgical complication (injury to the hemodynamic and respiratory system and brain, including major bleeding, tension pneumothorax, intracranial injury)
- Other reason, specify

Intra-operative complications possibly related to recruitment maneuvers:

- New hypotension (BPsys < 90mmHg or BPsys drop > 10mmHg, if BPsys < 90 before RM)
- New bradycardia (HR < 50bpm or HR drop > 20%, if HR < 50 before RM)
- New hypoxemia (SpO2 ≤ 92% or SpO2 drop > 5%, if SpO2 < 92% before RM)
- Other event, specify:

### *Post-operative variables*

The patients will be assessed daily between the first and the fifth day after surgery as well as on the last day before discharge from hospital. Clinical data and the presence of pulmonary and extra-pulmonary postoperative complications will be scored, the date of development of any complication documented (for definitions, see APPENDIX iii.).

The documentation will adhere to the timetable in APPENDIX iv.

- Continuation of non-invasive or invasive mechanical ventilation outside of the operation room directly after surgery; if yes: specify indication and duration, hours
- Any new requirement of non-invasive CPAP or NPPV; if yes: specify indication, duration and intensity
- Any new requirement of invasive mechanical ventilation; if yes: specify indication, duration and intensity
- ICU stay directly postoperative; if yes: specify reason

- Any new admission or readmission to the ICU at any time in the post–operative period; if yes: specify reason
- Postoperative nausea and vomiting (PONV)
- Physiotherapy and breathing exercises
- CAS  to evaluate mobility, see Appendix ii
- Wound healing: impaired wound healing can be defined as an interruption in the timely and predictable recovery of mechanical integrity in the injured tissue
- Surgical wound infection; if yes: specify location (superficial *or* deep, abscess, empyema *or* phlegmon )
- Return of bowel function
- Any need for anti–arrhythmic and vasoactive medication; if yes: specify
- Post–operative fluid requirements (crystalloids, artificial colloids, or albumin; specify type and amount since last assessment)
- Post–operative transfusion of packed red blood cells, fresh frozen plasma , plasma frozen within 24 hours (FP24), fibrinogen, cryoprecipitate, PPSB and platelets in the preceding six hours; if yes: specify type and number of units transfused since last assessment
- Respiratory rate and peripheral oxygen saturation in room air, beach chair position
- Presence or absence of airway secretion (ask patient to cough and subjectively evaluate presence and consistency of sputum; if yes: purulent *or* not)
- Noninvasive mean arterial pressure
- Heart rate (bpm)
- Tympanic temperature; °C
- VAS evaluation for dyspnea, thoracic and abdominal rest and incident pain
- Chest X–ray – not mandatory
- Bedside spirometry (FVC, FEV1) – not mandatory
- BUN, Creatinine, AST, ALT, Bilirubin, Hb, Platelets, PT, PTT, white blood cell count
- Date of hospital discharge

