| Spirometry (facultative)                                                                        |                |                             |                | X     | X     | X     | X     | X     | X                         |                            |
| Chest X-ray (facultative)                                                                       |                |                             |                | X     | X     | X     | X     | X     | X                         |                            |
| Routine laboratory tests (facultative)                                                          |                |                             |                | X     | X     | X     | X     | X     | X                         |                            |
| Blood sampling (special markers, facultative)                                                   |                |                             |                |       |       |       |       | X     |                           |                            |
| Post-operative fluids/transfusion requirement                                                   |                |                             |                | X     | X     | X     | X     | X     |                           |                            |
| Pulmonary complications (APPENDIX iii)                                                          |                |                             |                | X     | X     | X     | X     | X     | X                         |                            |
| Extra-pulmonary organ failure (APPENDIX iii)                                                    |                |                             |                | X     | X     | X     | X     | X     | X                         |                            |
| Adverse Events                                                                                  |                |                             |                | X     | X     | X     | X     | X     | X                         |                            |
| Date of hospital discharge                                                                      |                |                             |                |       |       |       |       |       | X                         |                            |

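### The post-operative transfusion item asks a six-hour yes/no question but counts units since the last assessment, and the same six-hour window does not fit the single end-of-surgery entry

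*Protocol*

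**What the plan says.** Section 7.2.4 of the Protocol collects transfusion in three lists.

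- **Pre-operative variables.** Blood products in the six hours before the pre-operative assessment, with type and amount.
- **Intra-operative variables.** The same window: "in the preceding six hours; if yes: specify type and number of transfused units/amount". In the same list, blood loss is "Blood loss; ml for whole duration of surgery", and urine output is treated likewise.
- **Post-operative variables.** The item reads "in the preceding six hours; if yes: specify type and number of units transfused since last assessment". The fluid item directly above it has no six-hour condition and asks only to "specify type and amount since last assessment".

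On timing, the post-operative text begins: "The patients will be assessed daily between the first and the fifth day after surgery as well as on the last day before discharge from" [...]. The Appendix iv timetable marks "Post-operative fluids/transfusion requirement" on each of days 1 to 5. It places intra-operative fluid balance and transfusion once, in the end-of-surgery column.

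Transfusion is not among the primary, secondary or other study parameters in 7.1. Section 8.2 has the remaining parameters summarised and compared between groups.

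**The concern.** The post-operative item holds two time windows in one line, and the shorter controls access to the longer. The count is conditional on a yes to the six-hour question, so red cells given at 20:00 before a 09:00 visit (13 hours) produce a no, and the request for units is never reached. A site that reads the second half of the line as governing would record those units. With about 90 centers expected (6.1), two sites could follow the same sentence and enter different data.

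The six-hour phrase suits the pre-operative list, where some limit on the look-back is needed. Its repetition in the other two lists has no stated reason, and the neighbouring items use windows that match the period being recorded.

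At stake is the completeness of a scheduled descriptive variable, and some uncertainty over whether a unit belongs to the pre-operative or the intra-operative record.

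**Working it through.** The Protocol gives no figure for transfusion capture, so there is none to reproduce. The check is how much of each recording period the six-hour window covers.

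**Inputs from the Protocol**
- Yes/no window: 6 h (7.2.4, post-operative and intra-operative lists).
- Count window, post-operative: back to the previous assessment (same line).
- Visits: daily, days 1 to 5 (7.2.4; Appendix iv).
- Intra-operative transfusion: one entry at end of surgery (Appendix iv).
- Expected duration of surgery: at least 2 h, no upper limit (6.2).

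**Assumption.** The Protocol does not say when transfusions occur within an interval. Even timing is taken first, then varied.

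**Post-operative item, six-hour question applied literally**

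One episode, interval of *g* hours, even timing: share missed = 1 − 6/*g*.

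| Interval *g* | Share missed |
|---|---|
| 12 h | 1 − 6/12 = 50% |
| 18 h | 1 − 6/18 = 67% |
| 24 h | 1 − 6/24 = 75% |

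With *k* independent episodes in a 24 h interval, a single yes opens the count for the whole interval. Units are therefore lost only if no episode falls in the last six hours: (1 − 6/24)^*k* = 0.75^*k*.

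| Episodes *k* | Probability that all units are lost |
|---|---|
| 1 | 75% |
| 2 | 0.75² = 56% |
| 3 | 0.75³ = 42% |
| 4 | 0.75⁴ = 32% |

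If transfusions cluster soon after surgery, the day 1 visit does worse. With an assumed exponential time of mean *m* hours, truncated to the interval, the share missed is [1 − exp(−(*g* − 6)/*m*)] / [1 − exp(−*g*/*m*)]. It runs from 62% (*g* = 12, *m* = 12) to 97% (*g* = 24, *m* = 6).

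If staff ignore the six-hour condition and record everything since the previous visit, the share missed is 0%.

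**Intra-operative item, read as a look-back from the end-of-surgery entry**

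Let *T* be the hours from the start of the intra-operative period to that entry. Pre-operative time inside the window = max(0, 6 − *T*). Intra-operative time outside it = max(0, *T* − 6).

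| *T* | Pre-operative hours inside | Intra-operative hours outside |
|---|---|---|
| 2 h | 4 | 0 |
| 4 h | 2 | 0 |
| 6 h | 0 | 0 |
| 8 h | 0 | 2 (2/8 = 25% of the period) |
| 10 h | 0 | 4 (4/10 = 40% of the period) |

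Only one of the two errors can occur in a given patient.

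**The case against.** A reader might infer that the post-operative item looks back only six hours and so misses about three quarters of transfusions. The documents do not support that. The same line asks staff to "specify type and number of units transfused since last assessment", so the defect is a contradiction between two windows, and units are lost only where the first is applied literally. The 75% further needs a 24 h interval, even timing and one episode. The Protocol gives no transfusion timing, and the interval before the day 1 visit starts at the end of surgery, so it need not be 24 h.

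It can also be said that Appendix iv governs the documentation and shows no six-hour limit. That is so, but the timetable fixes the days of recording and not the window, so it does not resolve the conflict.

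The case against the intra-operative half is stronger. The list is introduced as covering the intra-operative period, which argues against entering a unit given before induction. Its opening sentence also speaks of hourly measurement; if that covered transfusion, no intra-operative time would be missed. Against this, the list contains once-only items, and Appendix iv schedules transfusion once, at end of surgery. A reader might infer certain double counting with the pre-operative item. That does not follow: pre-operative data may be collected at the pre-anesthetic visit, before a late pre-operative unit is given. This half is therefore conditional.

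On consequence, the objection largely stands. Transfusion is not a named endpoint. Blood pressure, vasoactive drugs and fluids are recorded separately, as is massive transfusion where it leads to a protocol deviation.

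**Conclusion.** The point holds as a minor one. The post-operative item contradicts itself. Used as written at daily visits, it drops units whenever every transfusion since the last visit was given more than six hours before the present one. The fluid item above it points to the intended window.

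The loss ranges from 0% if sites follow the longer window, through 75% in the single-episode illustration, to above 90% in some early-clustering scenarios. No one figure should be quoted as the expected loss.

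The six-hour wording in the intra-operative list does not fit a single end-of-surgery entry unless the period happens to last six hours. This rests on reading the item as a look-back from that entry.

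The primary endpoint, sample size and interim design are unaffected. Only the descriptive transfusion data, and any between-group comparison of them under 8.2, are exposed.

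**What to change.** 1. **Post-operative list:** delete the six-hour phrase, so that the yes/no question and the count both run from the previous assessment. The gap between the two windows is then 0 h. State that, for day 1, the previous assessment is the end-of-surgery entry.
2. **Intra-operative list:** replace the six-hour phrase with a window from induction of anesthesia to end of surgery. The wording used for blood loss would not serve: 7.2.3 starts surgery at incision or trocar insertion, so units given between induction and incision would fall in neither list.
3. **Pre-operative list:** keep the six-hour look-back. For the two items to meet without gap or overlap, the pre-operative one has to be completed or updated just before induction.
4. **Data already collected:** the CRF is not among the documents. If it carried the six-hour condition, flag existing transfusion data as possibly incomplete.

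The cost is two short wording edits in the Protocol, one clarifying sentence for each of the day 1 and pre-operative items, matching CRF changes if needed, and a data flag. No visit or procedure is added.

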### 7.2.5 Blood and urine samples

Before, at the end of, and five days after surgery, blood samples (2 x 5 ml in EDTA, citrate and heparin) and urine samples will be collected and stored at –80°C for measurement of:

- Inflammatory mediators (cytokines, chemokines, other inflammatory proteins)
- Markers of lung injury (angiopoietin-2, surfactant proteins A and D)
- Specific markers of distal organ injury (e.g., cystatin C, NGAL)

## 8. STATISTICAL ANALYSIS

### 8.1 Descriptive statistics

Patient characteristics will be compared and described by appropriate statistics.

### 8.2 Analysis

The primary endpoint is a collapsed composite of postoperative pulmonary complications occurring in the first five days after surgery. These complications include aspiration pneumonitis, bronchospasm, mild respiratory failure, moderate respiratory failure, severe respiratory failure, development of acute respiratory distress syndrome, pulmonary infection, atelectasis, pulmonary edema caused by cardiac failure, pleural effusion, pneumothorax and new pulmonary infiltrates (for definition, see Appendix iii). Patients who develop a least one of the above mentioned complications are considered as meeting the primary endpoint.

Interim analyses for efficacy and futility will be conducted at 50% (N=956), 75% (N=1434) and 100% (N=1912) of the planned enrollment, as needed, using a non-binding group sequential design with gamma spending functions ( $\gamma = -4$  for each of  $\alpha$  and  $\beta$ ). The table below shows the  $\alpha$  and  $\beta$  spent over the trial, z-statistic boundaries for efficacy and futility, and boundary crossing probabilities under the alternative hypothesis ( $H_1$ ). The corresponding P-value boundaries for efficacy (futility in parentheses) at the 1st, 2nd and final looks, respectively, are  $P \leq 0.006$  ( $P > 0.82$ ),  $P \leq 0.015$  ( $P > 0.35$ ) and  $P \leq 0.044$  ( $P > 0.044$ ). The Figure below displays the z-statistic boundaries for efficacy/harm and futility as a function of accrued sample size.

| Table: Z-statistic boundaries and boundary crossing probabilities (under $H_1$ );
Power=0.80, $\alpha=0.05$ , gamma spending functions ( $\gamma = -4$ ), $p_1=.20$ , $p_2=0.15$ |                      |      |                        |                 |              |             |                                             |          |
|-------------------------------------------------------------------------------------------------------------------------------------------------------------------------------------|----------------------|------|------------------------|-----------------|--------------|-------------|---------------------------------------------|----------|
| Look                                                                                                                                                                                | Information Fraction | N    | Cumulative Alpha spent | Cum. Beta spent | Z- efficacy  | Z- futility | Boundary crossing probabilities under $H_1$ |          |
|                                                                                                                                                                                     |                      |      |                        |                 |              |             | Efficacy                                    | Futility |
| 1                                                                                                                                                                                   | 0.5                  | 956  | 0.006                  | 0.024           | $\geq 2.75$  | $< 0.225$   | 0.234                                       | 0.024    |
| 2                                                                                                                                                                                   | 0.75                 | 1434 | 0.018                  | 0.071           | $\geq 2.432$ | $< 0.929$   | 0.296                                       | 0.047    |
| 3                                                                                                                                                                                   | 1                    | 1912 | 0.05                   | 0.2             | $\geq 2.012$ | $< 2.012$   | 0.271                                       | 0.129    |

[figure not shown]

For the primary efficacy analysis rates of postoperative pulmonary complications will be compared between the two intervention groups and the odds ratio relative risks with corresponding 95% confidence levels interval will be calculated using logistic regression analysis.

With regard to the remaining parameters: Normally distributed variables will be expressed by their mean and standard deviation; non-normally distributed variables will be expressed by their medians and interquartile ranges. Categorical variables will be expressed as n (%). Student's *t*-test will be used to test groups of continuous normally distributed variables. Conversely, if continuous data is non-normally distributed, the Mann-Whitney-*U* test will be used. Categorical variables will be compared with the Chi-square test, Fisher's exact tests or, where appropriate, as relative risks. Time dependent data will be analyzed using a proportional hazard model adjusted for possible imbalances of patients' baseline characteristics.

Data analyses will follow an a priori documented statistical analysis plan which will be finalized before the end of data collection. By definition, only the analysis of the primary outcome is confirmatory, all other analyses are exploratory. The analysis strategy follows the intention-to-treat principle. The analysis will be undertaken blinded by a statistical expert. Statistical significance is considered to be at a *p*-value of 0.05. Where appropriate, statistical uncertainty will be expressed by 95% confidence levels.

The analysis will be performed with SPSS.

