#### 6.4 Sample size calculation

**Initial** sample size calculation was based on our primary hypothesis and primary study outcome, and was informed by data collected during a multicenter Spanish trial (ARISCAT) (see APPENDIX i) and a single-center, relatively small study reporting the effects of intraoperative higher PEEP and recruitment maneuvers on the incidence of postoperative desaturation, chest infection and bronchospasm in obese patients who underwent laparoscopic bariatric surgery.

These calculations indicated that 356 patients were required per group, assuming a two-sided significance level of 0.05 and a power of 80%, to detect the expected difference in postoperative pulmonary complications between the higher PEEP group of 30% and the lower PEEP group of 40% (risk ratio of 0.75). Assuming a dropout rate of 5%, **a total of 748 patients** (n=374 per group) were planned to be included into the study.

Sample size was re-estimated based on recommendations of the DSMB after data on the first 618 patients revealed that the incidence of the collapsed composite outcome was considerably lower than expected. In the revised calculations, the control group incidence was assumed to be 0.20 (instead of 0.40), and sample size was calculated to have 80% power at the overall 0.05 significance level to detect a relative risk (as originally planned) of 0.75. This design requires a maximum of 1912 patients, adjusting for the interim monitoring for efficacy and futility as described in section 8.2. Assuming a dropout rate of 5%, a total of 2013 patients need to be included into the study. East 6.0 interim monitoring software (Cytel, Cambridge, MA, USA) was used.

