### *Randomization arms*

Central randomization with the use of a permuted-block randomization list (block length 6) will be used. Before surgery patients will be randomly assigned 1:1 to mechanical ventilation with PEEP of 4 cmH2O without recruitment maneuvers (the “lower PEEP level”) or mechanical ventilation with PEEP of 12 cmH2O with the use of recruitment maneuvers (the “higher PEEP level”). If desaturation, defined as SpO2 ≤ 92% for > 1 min, occurs, rescue is performed according to the sub-section “Rescue Therapy”. Both strategies were chosen taking into account a recent national survey in France, most recent randomized clinical trials on mechanical ventilation of obese patients undergoing surgery and expert consensus, which was obtained during a meeting of the Respiration Subcommittee at Euroanaesthesia 2013 in Barcelona, Spain.

At each site at least two investigators will be involved: one who will be aware of the allocated intervention and collect intra-operative data; the other who will remain blinded to the intra-operative interventions and evaluate the outcomes, scoring postoperative pulmonary and extrapulmonary complications.

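### Section 8.2 pairs a final efficacy boundary of P ≤ 0.044 with a 95% interval and a 0.05 level, and does not link the reported relative risk to the stopping boundaries

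*Protocol*

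**What the plan says.** Protocol section 8.2 makes three statements about the primary outcome, the only analysis it calls confirmatory.

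- **The test.** Analyses at N = 956, 1434 and 1912 are run "using a non-binding group sequential design with gamma spending functions" with γ = −4 for both α and β. The efficacy boundaries are Z 2.75, 2.432 and 2.012, that is P ≤ 0.006, 0.015 and 0.044. At the last look a Z below 2.012 is on the futility side.
- **The estimate.** After the boundary table, the section says that "relative risks with corresponding 95% confidence levels interval will be calculated using logistic regression analysis".
- **The level.** The closing paragraphs put statistical significance at a p-value of 0.05 and add that, where appropriate, "statistical uncertainty will be expressed by 95% confidence levels". The primary outcome is not exempted.

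Section 8.2 also announces a separate statistical analysis plan, which was not available for this review.

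**The concern.** The first statement gives the final test a cut-off of 0.044. The second and third, on their ordinary reading, give a reader 1.96 SE and 0.05. A final P between 0.044 and 0.05 would then count as negative by the boundary table, positive by the general significance level, and would carry an interval that excludes 1. The authors would have to choose between these after seeing the result.

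A second issue arises if the trial stops early. The observed effect must be large to cross an interim boundary, so an estimate that ignores the stopping rule overstates benefit on average. By the protocol's own table, early stopping is the most likely route to a positive result under the alternative. Section 8.2 does not say how the effect would be reported in that case.

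**Working it through.** **Inputs.** Section 6.4: control rate 0.20, relative risk 0.75, 80% power, overall α 0.05, maximum N 1912. Section 7.2.1: 1:1 allocation, so 956 per arm. Section 8.2: looks, boundaries and spending functions.

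**Reproducing the design.**

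- α spent at information fraction t is 0.05 × (1 − e^(4t)) / (1 − e^4), giving 0.006, 0.018 and 0.05. The same form with 0.2 gives β spent of 0.024, 0.071 and 0.2. Both match the table.
- SE of the log relative risk at N = 1912: √[(0.80/0.20 + 0.85/0.15)/956] = √(9.667/956) = 0.1006. Expected final Z: ln(1/0.75)/0.1006 = 0.2877/0.1006 = 2.86.
- At look 1 the expected Z is 2.86 × √0.5 = 2.02, so the chance of crossing 2.75 is 1 − Φ(0.73) = 0.234, as printed.
- Early efficacy stopping under the alternative: 0.234 + 0.296 = 0.530.

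**Mismatch at the final look.** The two-sided P for Z = 2.012 is 0.0442, so the matching interval has level 1 − 0.0442 = 95.6%. A 95% interval uses 1.96. The conflict zone is 1.96 ≤ |Z| < 2.012.

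Example: 195/956 events in controls and 161/956 with higher PEEP.

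- Relative risk 0.826; SE = √(1/161 + 1/195 − 2/956) = 0.0962.
- Pooled Z = 1.998, P = 0.046: the boundary is not crossed.
- The 1.96 SE interval runs from 0.684 to 0.997 and excludes 1. The 2.012 SE interval runs from 0.680 to 1.002 and does not.

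**Simulation.** 2,000,000 binomial trials per scenario, 20% control rate, stated looks, both boundaries followed, pooled Z for the test, ordinary 95% log relative risk interval. Means are geometric.

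| True RR | Early efficacy stops | Mean RR reported | Share overstating | Coverage, early stops | Look-1 stops (coverage) | Coverage, all trials |
|---|---|---|---|---|---|---|
| 0.85 | 17.5% | 0.70 | 100% | 82% | 5.9% (59%) | 94.8% |
| 0.80 | 33% | 0.69 | 100% | 92% | 12.5% (81%) | 95.3% |
| 0.75 | 53.5% | 0.67 | 95% | 95.4% | 23.5% (90%) | 93.8% |
| 0.65 | 88% | 0.62 | 65% | 97.4% | 57% (96%) | 95.2% |
| 0.60 | 96% | 0.58 | 54% | 97.6% | 74% (97%) | 96.0% |

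At a true relative risk of 0.75, early stops report 0.62 on average at look 1 and 0.71 at look 2.

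The final Z falls in the conflict zone in 1.2% of trials at 0.75, 1.7% at 0.85 and 0.5% under the null. Counting only trials whose log relative risk interval itself excludes 1 gives 1.1%, 1.5% and 0.4%, because that interval and the pooled test are not algebraically identical. In the runs made, the reverse conflict (boundary crossed, 95% interval includes 1) did not occur.

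**The case against.** Several points on the other side are sound.

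- **The conflict is narrow.** The zone is 0.052 wide in Z. With 191 control events, moving from 157 to 158 events in the other arm takes Z from 2.015 to 1.954, so the zone is narrower than one event.
- **An unadjusted interval is an inference.** Section 8.2 names 95% and logistic regression; it does not say 1.96 or unadjusted. The 0.05 could be meant as the overall level that the boundaries already spend.
- **Adjusted estimation is often left to the SAP.** Its absence from the protocol is therefore not an error in itself. Bias after early stopping is a general property of sequential designs.
- **The repeated interval has a price.** Its overall coverage at 0.75 is 98.8%, further from 95% than the ordinary interval's 93.8%.

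A reader might also infer that every early stop must exaggerate the effect. The figures do not support that: at true relative risks of 0.65 and 0.60, about 35% and 45% of early stops do not. Nor do intervals after early efficacy stops generally undercover: at 0.75 the two interim looks together cover 95.4%, because look 2 (99.8%) offsets look 1 (90%). Early stopping is possible at two looks, not three, since the third is the final analysis.

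What remains is that section 8.2 prints 0.044 and 0.05 for the same final analysis, with an interval tied to neither. An SAP may say which governs, but the protocol would still contain both.

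**Conclusion.** The point holds as a conflict within section 8.2 that should be reconciled, with a recommendation on early stopping attached. Its practical size is modest.

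- The disagreement between interval and test affects about 1.2% of trials at a true relative risk of 0.75 and 1.7% at 0.85. If it occurs, it concerns the trial's main conclusion.
- After an early efficacy stop the unadjusted relative risk overstates benefit on average (0.67 for a true 0.75). It does so nearly always when the true value is 0.75 or weaker, but not always when the effect is stronger.
- Overall coverage is 93.8% to 96.0% across the scenarios shown. Among efficacy stops, the shortfall is mainly at look 1 and at effects weaker than planned.

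These figures assume an ordinary ±1.96 SE interval, a 20% control rate, equal arms, looks exactly at the stated N, and futility boundaries that are followed and applied to |Z|. The protocol makes futility non-binding, so actual stopping could differ.

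**What to change.** Amend section 8.2, and align the SAP with it, before any interim result is known:

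1. State that the group sequential boundary at the look where the trial ends governs the primary test, and that the general 0.05 level applies to the other analyses.
2. At the final look, report the primary relative risk with 2.012 SE on the log scale (a 95.6% interval). Base it on the same statistic as the test so that the two cannot disagree.
3. If the trial stops early for efficacy, report a sequentially adjusted interval and a bias-adjusted estimate beside the observed relative risk. One option is the repeated confidence interval with the printed critical value, 2.75 or 2.432. Stage-wise ordering is an alternative at looks 2 and 3, but at look 1 it equals the ordinary interval and changes nothing.

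The cost is a few sentences, with no added patients or data. On the log scale the interval widens by 2.012/1.96 = 2.7% at the final look. The repeated interval would be 24% wider at look 2 (2.432/1.96) and 40% wider at look 1 (2.75/1.96). It is conservative, and the text should say so. The final-look change resolves the conflict; the choice of method after an early stop is partly a matter of preference and can be detailed in the SAP.
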